### Study Outline

This is a prospective dose-finding study of esmolol aiming to attenuate the sympathetic surge associated with severe TBI in adults. The setting is the 48-bed mixed ICU of Southmead Hospital, Bristol, a 996-bed teaching hospital in the southwest of England, and a major trauma center serving an adult population of approximately 2.3 million. On average, the ICU admits more than 130 patients with severe TBI annually.

The primary objective is to define a treatment dosage escalation schedule for esmolol for use in adults early (< 24 h) after severe TBI that balances the potential benefit of early exposure to beta-blockade with the ability to maintain adequate CPP. A reduction of heart rate of at least 15% from preinfusion baseline will be used as an indicator of clinically significant beta-blockade.

A group sequential adaptive model-based design (the CRM) will be used to determine the maximum tolerated dosage schedule for esmolol, defined as the highest dosing regimen associated with an acceptable level of toxicity. For the purpose of this study, this is taken to be a probability of dose-limiting toxicity of 10%. Dose-limiting toxicity is defined as failure to maintain CPP above the minimum recommended by Brain Trauma Foundation guidelines (60 mm Hg), despite standard interventions including vasopressors and the protocolized deescalation of the esmolol infusion such that withdrawal of esmolol is required, or the occurrence of a serious adverse event mandating withdrawal of the esmolol infusion.

Secondary objectives are to identify the effects of esmolol on organ function and to record clinical outcomes including mortality and function at 6 months. Exploratory objectives are to monitor the effects on biomarkers of sympathetic nervous system activity and to gather data to inform the design of a randomized controlled trial to establish feasibility and efficacy.

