### Statistical Analysis

Inability to maintain CPP in the presence of esmolol was chosen as the primary definition of toxicity based on the known importance of adequate blood pressure for prevention of secondary brain injury [19]. The maintenance of adequate CPP as a key goal of therapy is also familiar to clinicians practicing in the field of neurointensive care.

Only data from esmolol-treated patients will be used in statistical analysis. Esmolol-treated patients are those who meet all inclusion criteria and no exclusion criteria, receive any dosage of esmolol within 2 h of confirmation of eligibility and 24 h of injury, and do not withdraw consent for use of data prior to use of that data in CRM analysis.

A one-parameter logistic model, initialized with skeleton parameters as per Table 2, will be used for the CRM modeling, with estimated probabilities revised as data emerge. This likelihood modeling algorithm will identify a maximum tolerated dose escalation schedule, with a defined prior reasoned target toxicity level, or “acceptable” toxicity rate (*θ*), of 10% with an indifference level of 2 percentage points for decision making. The weighting afforded to the pretrial logistic model on estimated probabilities will be revised as trial data sequentially emerge.

**Table 2 Tab2:** Predefined dose levels for esmolol infusion

Dose level	Starting dosage (mcg.kg.min^−1^)	Increment (mcg.kg.min^−1^)	Estimated prior probability of dose-limiting toxicity
1	5	2.5	0.01
2	10	5	0.04
3	16	8	0.07
4	25	12.5	0.10
5	35	17.5	0.15
6	46	23	0.20
7	62	31	0.25

Cohort size of three will be used. In the absence of dose-limiting toxicity, an increase in the dosage escalation schedule will be considered by the trial management group after the last patient in a cohort has completed the esmolol intervention period. Dosage escalation cannot be by more than one level and, as an additional safety measure, the dosage will not be escalated until the second cohort has completed intervention. Dosage deescalation will be considered after each dose-limiting toxicity and is unrestricted. Dosage level changes are subject to sponsor approval with oversight of dosage decision making the responsibility of the Steering Committee comprising independent expert and lay members. The Steering Committee is also responsible for monitoring study conduct and safety in lieu of formal Data Monitoring and Ethics Committee given the setting and design of the study.

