The planned sample size of 24 esmolol-treated patients was determined in a pragmatic manner based on estimated recruitment rates following a test screening period in the ICU that were compatible with the timeline required by the funder and on the expected small information gain for additional patients over and above the target. This allows testing of up to seven dosage levels (Table 2).

In analysis of secondary and exploratory outcomes continuous variables will be summarized by descriptive statistics (mean and standard deviation, minimum, median, maximum, and interquartile range) and categorical data will be summarized in terms of frequency and percentage.

The Sequential Organ Failure Assessment will be reported as both daily total and by variable, excluding neurological assessment. Mortality outcomes will be analyzed using Kaplan–Meier survivorship. Length of stay and duration of mechanical ventilation will be analyzed using time to event Kaplan–Meier analyses. Both the number of patients with a bloodstream infection and the total number of bloodstream infections in ICU will be reported. The eGOS will be reported by category and dichotomized into favorable (eGOS 4–8) and unfavorable (eGOS 1–3) outcome, differentiating between patients who are independent at home or who are not. Quality of life (EQ-5D-5L) will be reported as the EQ-5D index and by each dimension.

Blood biomarkers (troponin, glucose, lactate, and International Normalized Ratio) will be reported for each day of the esmolol infusion. The incidence of safety outcomes is the number of events per calendar day of esmolol infusion (i.e., with at least 12 h of infusion) and will be reported as an overall incidence and by category. The dosage of vasopressor will be reported as noradrenaline equivalents in micrograms per kilogram per minute, with a correction factor of 10 used to convert from metaraminol.

The rate of recruitment reported as percent of screened population enrolled and as % of eligible population enrolled by month. Noncompliance with protocol, defined according to Sponsor’s Standard Operating Procedure as any breach of Good Clinical Practice or protocol, will be presented as total number of events and number of patients with episodes of noncompliance.

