## Conclusions

Here, we present the protocol for a dose-finding study of esmolol for early beta-blockade after severe TBI using the CRM. Both the drug and study design are novel in this setting. This study will determine a dosage schedule for esmolol that can be tested for benefit in adults with severe TBI.

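### Level 7 can only ever receive the last three patients, so a top-level or no-toxicity result cannot establish a maximum tolerated schedule, although the plan says one will be identified

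*Protocol article*

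**What the plan says.** All the design elements are in the protocol article, mainly under Statistical Analysis.

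- **Size and cohorts:** "The planned sample size of 24 esmolol-treated patients was determined in a pragmatic manner", and "Cohort size of three will be used".
- **Escalation:** "Dosage escalation cannot be by more than one level", and "the dosage will not be escalated until the second cohort has completed intervention". Escalation is considered when a completed cohort shows no DLT.
- **Levels:** Table 2 lists seven, with prior DLT probabilities 0.01, 0.04, 0.07, 0.10, 0.15, 0.20 and 0.25. The sample size paragraph adds: "This allows testing of up to seven dosage levels (Table 2").
- **Model:** a one-parameter logistic continual reassessment method (CRM), target 10%, indifference level 2 percentage points. "This likelihood modeling algorithm will identify a maximum tolerated dose escalation schedule".
- **Claim:** Study Outline describes the target as "defined as the highest dosing regimen associated with an acceptable level of toxicity", set there at a 10% DLT probability. Conclusions says: "This study will determine a dosage schedule for esmolol that can be tested for benefit in adults with severe TBI".

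**The concern.** The cohort rules use up the whole sample on the way to level 7. A trial that climbs the ladder cleanly ends at the moment when the top level has produced its first and only three observations. The plan nevertheless states without qualification that the algorithm will identify a maximum tolerated schedule at 10% toxicity.

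If level 7 is named on 0/3, the 10% statement about it rests almost wholly on extrapolation from lower levels through a one-parameter curve. If there is no DLT in the whole trial, the data put no upper limit on tolerability within the range tested. The named schedule goes forward to the later trials of the programme. A result meaning only that the levels ran out should not be carried forward as an established maximum.

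**Working it through.** **Reproducing the plan's figure.** 24/3 = 8 cohorts. The fastest permitted path is levels 1, 1, 2, 3, 4, 5, 6, 7, so seven levels can be visited, as stated. Patients per level are 6+3+3+3+3+3+3 = 24. Level 7 is open only to cohort 8, and only if every review from the second cohort on leads to escalation. This reads the run-in cohort of three (section on the rationale for the CRM) as part of the 24.

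**Assumptions the article does not supply.** Logistic intercept 0, 1, 3 or 4. Pure likelihood fit, or a normal prior on the log slope with SD 0.5, 1.16 or 2. Final choice by the estimate nearest 10%, or by the highest estimate not above 10%. Each fit uses the Table 2 skeleton, 0/21 at levels 1 to 6 and t/3 at level 7.

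**t = 0.**
- With no DLT in 24 patients the likelihood has no maximum: the fitted probability tends to 0 at every level. Level 7 is then named because there is no level 8.
- With a prior and the plug-in estimate (intercepts 0, 1 and 3), level 7 is named in 8 of 9 settings. The exception is intercept 0 with SD 0.5, which gives level 6.

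**t = 1.**
- The likelihood estimate at level 7 is 10.7% to 11.7% across the intercepts, against 7.2% to 7.9% at level 6. Level 7 is nearest to 10% and inside 10% ± 2 points, so nearest-to-10% selection names level 7.
- A strict cut at 10% on the same fit gives level 6.
- Posterior-mean estimation gives level 5 or 6 in all 12 settings (four intercepts, three prior SDs).
- Plug-in estimates are mixed. For example, intercept 3 with SD 1.16 gives 9.3% at level 7, which is named, while intercept 0 gives level 5 or 6.

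**t = 2.** The likelihood estimate at level 7 is 18.9% (intercept 3), and level 5 is chosen.

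**How well three patients discriminate, once level 7 is reached.** P(0/3) = (1−p)³ and P(0/3 or 1/3) = (1−p)³ + 3p(1−p)².

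| True DLT rate at level 7 | P(0/3) | P(0/3 or 1/3) |
|---|---|---|
| 10% | 0.729 | 0.972 |
| 25% (its Table 2 value) | 0.422 | 0.844 |
| 40% | 0.216 | 0.648 |

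The exact one-sided 95% upper bound after 0/3 is 1 − 0.05^(1/3) = 0.632.

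**How often level 7 is reached.** In exact enumeration of all eight-cohort paths, level 7 was reached only with no DLT in the first 21 patients.
- *Table 2 true:* 0.99⁶ × 0.96³ × 0.93³ × 0.90³ × 0.85³ × 0.80³ = 0.154. Level 7 is named in 0.154 × 0.422 = 6.5% of trials (0/3 only) to 0.154 × 0.844 = 13.0% (0/3 or 1/3).
- *Lower levels safe (assumed 1, 1, 2, 3, 4, 5% at levels 1 to 6):* 0.99⁹ × 0.98³ × 0.97³ × 0.96³ × 0.95³ = 0.595. If level 7 is truly 25%, it is named in 0.595 × 0.422 = 25% to 0.595 × 0.844 = 50% of trials. If it is truly 10%, the figures are 43% to 58%.

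**Other levels.** In simulation with Table 2 true, intercept 3 and nearest-to-10% selection among tried levels, the named level had only three patients in 39% to 44% of trials, depending on the prior.

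**The case against.** The strongest reply has four parts.

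1. *The seven-level sentence is literally true, and a condensed article may leave final-decision details to the full protocol or analysis plan.* This stands as far as it goes. A reader might infer that the seven-level figure is wrong, and it is not. But the three-patient ceiling follows from numbers and rules that the article itself fixes, and no analysis plan wording can alter it while those rules hold. The unqualified promise to identify a maximum is also the article's own. The Discussion concedes a pragmatic sample size, but not this consequence.

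2. *Selection after 1/3 is not determined.* This stands. A reader might infer that the design would usually name level 7 on 1/3. That holds for the likelihood fit with nearest-to-10% selection, but mostly fails under posterior-mean estimation or a strict 10% cut. The article gives no intercept, prior or final cut. Its reference to weighting the pretrial model also suggests that some prior may be used, so a pure likelihood fit with no maximum is a possibility, not the established plan.

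3. *The whole trial protects better than the last cohort does.* This stands. A reader might infer that the design cannot tell an acceptable top level from an unacceptable one. That goes too far: reaching level 7 needs a clean run below it, which happens in about 15% of trials under Table 2. Level changes also pass through the trial management group and need sponsor approval, with Steering Committee oversight.

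4. *Borrowing across levels is the purpose of a CRM, so few patients at one level is no defect in itself.* This stands for levels inside the ladder, and it is why a minimum number of patients per named level is not recommended. A six-patient threshold would leave about 40% of simulated trials without a named maximum. It does not rescue the top level or a no-DLT trial, where no higher level or no toxicity bounds the answer.

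**Conclusion.** The point holds in a limited form. That level 7 can have at most three patients, with no cohort left to act on them, is exact. That 0/3 there leads to level 7 being named holds in nearly all settings tried. Such a result would arise 73% of the time, once level 7 is reached, at a true DLT rate of 10%, and 42% of the time at 25%. It is compatible with a rate up to 63%. It cannot establish a maximum tolerated schedule at 10%, and nor can a trial with no DLT.

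The practical size depends on the unknown toxicity curve. If Table 2 is true, level 7 is named in about 7% to 13% of trials. If levels 1 to 6 prove safe and level 7 is truly 25%, the illustration above gives 25% to 50%. The documents do not support the broader readings that 1/3 would usually suffice, or that the design as a whole has no discrimination. These conclusions rest on the run-in being inside the 24, and on the intercepts, priors and selection rules listed above.

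**What to change.** Keep the patients, dosing and escalation rules unchanged, and limit what may be concluded.

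1. Add to the final decision rule: if level 7 is selected, or no DLT occurs in the trial, the result is reported as *highest level tested; maximum tolerated schedule not established*. Give the raw DLT count at that level and the model-based 95% interval for its DLT probability.
2. Reword the sample size paragraph of Statistical Analysis. Seven levels can be visited only if every review from the second cohort on leads to escalation, and level 7 then has exactly three patients.
3. For any other selected level, report the number treated at it and the 95% interval, with no six-patient threshold for naming it.

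The cost is wording. The downside is that a top-level or no-DLT result is labelled provisional instead of as a maximum tolerated schedule. With Table 2 as the truth, a level 7 selection arises in about 7% to 13% of trials and a trial with no DLT in 0.154 × 0.75³ = 6.5%. The two largely overlap.

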### Pharmacovigilance

Patients admitted to intensive care following severe TBI are critically ill and have a high baseline risk of complications of illness and of death. Medical occurrences that meet the definition of adverse events and adverse reactions may be expected features of critical illness requiring ICU care. All adverse events and adverse reactions will be considered in the context of the individual patient’s clinical condition and the natural history of severe TBI. Those who are considered by the chief investigator (or medically qualified designate) to be consistent with the patient’s critical illness do not require recording or reporting, unless the investigator considers they may relate to participation in the trial. All serious adverse events and serious adverse reactions both expected and unexpected will be recorded. For the purpose of this study, the Reference Safety Information is the Summary of Prescribing Characteristics for Brevibloc Premixed 10 mg/mL solution for infusion (Baxter Healthcare Ltd) [21].

Secondary and exploratory outcomes include assessment of organ function and significant hemodynamic side effects of esmolol infusion as a means of capturing additional safety information in the patient population. Protocol-based guidance is available for the management of specific adverse events (e.g., bradycardia with hemodynamic compromise). The primary responsibility for management of adverse events lies with the treating clinician.

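### Kaplan–Meier is prescribed for length of stay and ventilation without treating death as a competing event; cumulative incidence would fit these outcomes better

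*Protocol article*

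**What the plan says.** The Statistical Analysis section of the protocol article fixes the method in two consecutive sentences: "Mortality outcomes will be analyzed using Kaplan–Meier survivorship", then "Length of stay and duration of mechanical ventilation will be analyzed using time to event" Kaplan–Meier methods. The Secondary Outcomes section applies these to mortality at three horizons (ICU, acute hospital, 6 months), to ICU and acute hospital length of stay, and to duration of mechanical ventilation.

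On the risk of death, the Pharmacovigilance section says that these patients "have a high baseline risk of complications of illness and of death". The stopping rules under Study Intervention list death and withdrawal of life-sustaining treatment among the reasons for ending the infusion, so deaths within the first days are foreseen. The article gives no mortality rate and no expected length of stay.

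Two other statements matter. The Statistical Analysis section also has a general rule that categorical secondary outcomes are summarised as counts and percentages. The Study Outline gives, as an exploratory objective, gathering data to inform the design of a randomised trial.

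**The concern.** A patient who dies in the ICU can no longer be discharged alive or come off the ventilator. Kaplan–Meier has one event and one kind of censoring, and it assumes that a censored patient has the same future chance of the event as those still under observation. In one hospital, nearly every stay will be seen to end, with transfers a minor exception. The main candidate for censoring in the stay and ventilation curves is therefore death, for which that assumption is plainly false.

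Two obvious ways of applying the method lead to different difficulties:

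- **Deaths censored at death.** The dead are treated as still able to leave, so the estimated proportion discharged alive or liberated is too high and the median time too short.
- **Death counted as the end of the stay.** The curve is a correct estimate of time to any exit, but an early death scores the same as an early recovery. A short median stay could then mean either.

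What is at stake is how these summaries are read, including by those who use them to plan the later studies in the programme.

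**Working it through.** **The plan's own figure.** The only stated number near this point is the sample size: "The planned sample size of 24 esmolol-treated patients was determined in a pragmatic manner". It agrees with the design. "Cohort size of three will be used", and the first escalation is held back: "the dosage will not be escalated until the second cohort has completed intervention". That gives two cohorts at level 1 and one at each of levels 2 to 7, or 3 × (2 + 6) = 24. The point below does not depend on this figure, which shows only how small the group is.

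**Inputs for the illustration, all assumed.** The share p of ICU exits that are deaths is 10%, 20%, 30% or 40%. The mean time to any exit is m = 14 days. Hazards are constant: death p/m and live discharge (1 − p)/m. The time point is t = 28 days.

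**Formulas for live discharge.**

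- Cumulative incidence with death competing: (1 − p) × [1 − exp(−t/m)]
- 1-KM with deaths censored: 1 − exp[−(1 − p) t/m]
- Any exit: 1 − exp(−t/m)

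**Example, p = 30%.** Cumulative incidence is 0.7 × (1 − e^−2) = 0.7 × 0.865 = 0.605. 1-KM is 1 − e^−1.4 = 0.753. The difference is 0.148, or 15 points.

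| ICU mortality (assumed) | Discharged alive by day 28, cumulative incidence | 1-KM, deaths censored | Overstatement, points | Median days, cumulative incidence | Median days, KM |
|---|---|---|---|---|---|
| 10% | 0.778 | 0.835 | 6 | 11.4 | 10.8 |
| 20% | 0.692 | 0.798 | 11 | 13.7 | 12.1 |
| 30% | 0.605 | 0.753 | 15 | 17.5 | 13.9 |
| 40% | 0.519 | 0.699 | 18 | 25.1 | 16.2 |

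The medians are −m ln[1 − 0.5/(1 − p)] for cumulative incidence and m ln 2/(1 − p) for Kaplan–Meier. The probabilities depend on t and m only through t/m. The same overstatement therefore applies to ventilation or hospital stay at twice the mean time to exit, whatever that mean is.

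**If any exit is the event.** The day-28 value is 1 − e^−2 = 0.865 and the median is 14 × ln 2 = 9.7 days in all four rows. There is no bias for time to any exit, but the curve cannot distinguish 10% mortality from 40%.

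**Early deaths.** A simulation of 5,000 runs with n = 24 used deaths at a mean of 5 days and live discharge at a mean of 16 days (gamma times, shapes 1.5 and 3). With deaths censored, the day-28 overstatement of live discharge was 9, 17, 26 and 35 points for the same four mortality values.

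**ICU mortality, if discharges were censored.** Under constant hazards the cumulative incidence of death at day 28 is p × [1 − exp(−t/m)] = 0.086, 0.173, 0.259 and 0.346. 1-KM is 1 − exp(−p t/m) = 0.181, 0.330, 0.451 and 0.551, which is 9, 16, 19 and 20 points too high. In the early-death simulation the excess is only 2, 3, 5 and 6 points.

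**The case against.** The strongest reply is that the article does not say how deaths are handled, and that event and censoring rules are commonly left to the full protocol or analysis plan. This is correct and limits the claim. A reader might infer that the planned estimates are certainly biased, but the documents do not support that. Kaplan–Meier is valid for time to any exit, which is literal length of stay and relevant to bed use. There is also a third convention, in which deaths are kept in the risk set to the end of follow-up. With complete follow-up of the stay, 1-KM then equals the cumulative incidence of live discharge. The bias arises only if deaths are censored when they occur.

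A reader might also infer that ICU and hospital mortality will be inflated. The article never says that patients are censored at discharge. Vital status is followed to 6 months, so one survival curve to that point is a natural reading and is sound. The counts-and-percentages rule could also cover in-unit mortality. This part is therefore a precaution, although the specific sentence does assign Kaplan–Meier to mortality outcomes without exception.

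A third tempting inference is that errors here would pass directly into the sample size of the next trial. The article says only that data will help inform a later design. These outcomes are descriptive, in a single arm with no control group and no test. With n = 24, the 95% half-width for proportions of 0.52 to 0.78 is 1.96 × √[p(1 − p)/24], about 17 to 20 points, as large as most of the illustrated bias.

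What remains is that the article does more than omit detail. It names a method for stay and ventilation whose usual applications either misstate live discharge or do not separate it from death, in patients it describes as being at high risk of death. Sampling error in a small group is no reason to accept an avoidable systematic error as well.

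**Conclusion.** The point holds in conditional form. For length of stay and ventilation, Kaplan–Meier with deaths censored overstates live discharge and liberation by about 6 to 18 points at day 28, for assumed ICU mortality of 10% to 40%, constant hazards and a mean stay of 14 days. The early-death scenario gives 9 to 35 points. With death counted as an exit there is no estimator bias, but death and recovery are merged. Every one of these magnitudes rests on assumed mortality, stay and timing. They show direction and order of size and do not predict this trial's results.

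Kaplan–Meier is appropriate for survival to 6 months. The primary outcome, the dose-finding model and the dose decisions do not use these outcomes and are unaffected. The change is worth making for accurate description; the validity of the trial does not depend on it.

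**What to change.** Amend the two sentences in Statistical Analysis, or settle the matter in the analysis plan before the analysis is run:

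1. Report ICU and hospital length of stay as the cumulative incidence of live discharge, and duration of ventilation as the cumulative incidence of liberation from ventilation. Treat death as a competing event in both (Aalen–Johansen) and show the death curve alongside. With complete follow-up this is simply the number discharged alive, or liberated, by each day divided by the number treated.
2. Report ICU and hospital mortality as proportions with exact 95% intervals, not as Kaplan–Meier curves censored at discharge.
3. Keep Kaplan–Meier for survival from enrolment to 6 months.
4. If time to any exit is also wanted as a measure of bed use, label it as such.

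The cost is a few lines of text and a standard routine. The listed outcomes already require the dates of death, discharge and end of ventilation, so no new data are needed.

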### Study Intervention

Open-label esmolol is given as a continuous intravenous infusion at a dosage of 2.5–200 mcg.kg.min^−1^ titrated using a predefined dosage escalation schedule to achieve a heart rate reduction of ≥ 15% from baseline with CPP maintained above 60 mm Hg. The target heart rate will be set as the rolling mean over the preceding 5 min to avoid overshoots. Baseline is defined as the mean heart rate in the 4 h preceding confirmation of eligibility. The minimum permitted target heart rate will be 60 beats per minute, even if this is less than 15% reduction from baseline; the maximum will be 100 beats per minute, even if this is more than a 15% reduction from baseline. Actual body weight at the time of enrollment in the study (estimated or known) will be used for dosage calculations.

A starting dosage is defined for each cohort, with dosage increments for that cohort being 50% of the starting dosage. The dosage is reviewed and adjusted every 30 min as required to achieve the target heart rate (± 5 beats per minute). Titration to achieve heart rate control for short lived stimulating procedures (e.g., tracheal suction, positioning, portable chest X-ray) is not required. The infusion should be continued during procedures including surgery or within hospital transfers for imaging.

When the infusion is restarted after temporary suspension (e.g., for bradycardia or if heart rate maintained in target range without need for infusion), the starting dosage for that level will be used with increments every 30 min as required. The infusion should not be restarted after a temporary suspension until the heart rate exceeds the minimum target rate (or 60 beats per minute) for more than 15 min.

Esmolol infusion continues according to study protocol until one of the following stopping rules is met:Ninety-six hours from start of infusionHeart rate target achieved without esmolol for > 12 hDose-limiting toxicityDeath or withdrawal of life-sustaining treatmentRequest of participant, legal representative, or treating clinicianICU discharge or transfer to nonparticipating ICU

The esmolol is weaned in steps of 5–10 mcg.kg.min^−1^ every hour from 96 h to avoid rebound tachycardia. In the event of dose-limiting toxicity, it may be reduced more quickly or stopped immediately. In the event of ICU discharge or transfer to a nonparticipating ICU, the infusion will be reduced at a rate calculated to ensure at least 2 h without esmolol infusion prior to discharge.

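### The three hemodynamic safety outcomes are defined solely as events per infusion day; the number of patients affected should be reported beside that rate

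*Protocol article*

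**What the plan says.** The Exploratory Outcomes section names three safety items, each as an incidence: bradycardia, second- or third-degree heart block, and clinically significant hypotension. All three carry the same qualifier: the episode must have required some intervention other than a reduction of esmolol.

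The Statistical Analysis section then defines that incidence: "The incidence of safety outcomes is the number of events per calendar day of esmolol infusion". It adds which days count and how the result is broken down: "i.e., with at least 12 h of infusion) and will be reported as an overall incidence and by category".

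Two other recurrent outcomes in that section are treated differently. For bloodstream infection, "Both the number of patients with a bloodstream infection and the total number of bloodstream infections in ICU will be reported". Noncompliance "will be presented as total number of events and number of patients with episodes of noncompliance".

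A general sentence on secondary and exploratory outcomes says that "categorical data will be summarized in terms of frequency and percentage". It does not say whether the unit is the patient or the event.

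The Study Intervention section provides for resuming esmolol at the level's starting dosage, in a sentence that begins "When the infusion is restarted after temporary suspension (e.g., for bradycardia". The infusion may run for up to 96 hours.

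**The concern.** A rate of events per day is fixed by two totals, events and days. It carries no information on how the events are spread over patients. The spread matters here because a patient may have a treated episode, continue or resume esmolol, and have another.

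Two stated purposes call for a figure per patient. The Pharmacovigilance section relies on these outcomes for additional safety information in this population. The Study Outline wants data that will inform the design of a randomized trial. Designers of such a trial would ask what proportion of treated patients needed an added intervention for bradycardia, heart block or hypotension. The planned rate does not answer that. Toxicity in the dose-finding model is also a probability per patient, so a rate per day cannot be set directly beside it.

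The plan already reports patients as well as events for two other outcomes that can recur. These three are the exception.

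**Working it through.** The article states no expected safety rate, so there is no planned figure to reproduce. The check is whether the defined measure can tell apart two situations that differ in the number of patients affected.

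**Inputs from the article**
- Patients: 24. "The planned sample size of 24 esmolol-treated patients was determined in a pragmatic manner".
- Maximum infusion time before weaning: 96 h, taken as 4 days per patient.
- Measure: events divided by infusion days, counting days with at least 12 h of infusion.

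**Assumptions (not in the article)**
- Every patient contributes the same number of countable days: 4 in the main case, with 3 and 2 as alternatives.
- 4 events of one type in total.

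**Formulas**
- Rate = total events / total countable days.
- Patient proportion = patients with at least one event / 24, with an exact (Clopper-Pearson) 95% interval.

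**Main case.** Total days = 24 × 4 = 96. Rate = 4 / 96 = 0.042 per day.

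| How the 4 events fall | Rate per day | Patients affected | Exact 95% CI |
|---|---|---|---|
| All in one patient | 0.042 | 1/24 = 4.2% | 0.1% to 21.1% |
| One each in four patients | 0.042 | 4/24 = 16.7% | 4.7% to 37.4% |

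**Fewer days.** With 3 days each, 4 / 72 = 0.056 per day; with 2 days each, 4 / 48 = 0.083 per day. The rate moves, but it is still identical for the two rows of the table.

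**One cohort of three.** Three patients with 4 days each give 12 days. Three events give 3 / 12 = 0.25 per day, whether 1 of 3 or 3 of 3 patients were affected.

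**Where exact equality fails.** The two situations share a rate only if total days are equal. Suppose four patients each have one event and stop before completing 12 h, so that they add no countable days, and suppose those events are still counted. The remaining 20 patients give 20 × 4 = 80 days, and the rate is 4 / 80 = 0.050 rather than 0.042 per day. The rate then differs because the denominator changed. It still does not show how many patients were affected.

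**The case against.** The strongest reply has five parts.

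1. **The outcomes are narrower than raw physiology.** A reader might infer that every dip of the heart rate below 50 counts, that a rate hovering near that limit inflates the numerator, and that repeat events are inherent in the 30-minute dose review. The Exploratory Outcomes section does not support this. An episode handled only by lowering esmolol is not an outcome event. The restart provision shows that recurrence is possible, not that it will be frequent. This part of the reply stands, and the point here rests only on possibility.

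2. **The general sentence on frequency and percentage may cover a patient table.** It could be read that way, so one cannot say that patient counts will never appear. But it names no unit, and the specific definition of incidence governs these three outcomes. The explicit patient counts for bloodstream infection and noncompliance show how the article writes when it intends them.

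3. **The rate is defensible.** Infusion time varies under the stopping rules, and a rate per day allows for that where a plain patient percentage does not. This stands. Replacing or demoting the rate would be a preference, not a correction.

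4. **Patient-level safety is already central.** Dose-limiting toxicity is judged per patient and drives the model, and all serious adverse events are recorded. This stands for events that force withdrawal of esmolol. Events managed without withdrawal are not captured as dose-limiting toxicity.

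5. **No interval for the rate is planned.** A reader might object that an interval treating events as independent would be too narrow. The article specifies only descriptive summaries here, so that would criticise an analysis the plan does not contain.

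**Conclusion.** The point holds as a reporting gap in exploratory safety outcomes. As defined, the incidence of treated bradycardia, heart block and hypotension does not show how many of the 24 patients were affected. The same article already reports both patients and events for two other outcomes.

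The illustration, 0.042 per day for either 4.2% or 16.7% of patients, rests on an assumed 4 events and equal infusion time. The documents give no expected rate, so the actual size is unknown. If events rarely recur within a patient, the number of events will be close to the number of patients, and little would be lost. That the rate cannot separate the two situations when total days are equal does not depend on the assumed numbers.

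A reader might infer that the dose finding or the safety of the trial is compromised. The documents do not support that: dose decisions rest on dose-limiting toxicity per patient, and neither the sample size nor the primary conclusion depends on these outcomes.

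**What to change.** Keep the events-per-day rate as defined. Add one sentence to the Statistical Analysis section: for each of the three safety outcomes, the number and percentage of esmolol-treated patients with at least one event will be reported alongside the rate. An exact 95% confidence interval for the percentage is optional.

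The cost is that sentence and one more column in the safety table. The data are the same as those needed for the event count, and no patients or procedures are added. The patient percentage does not adjust for differing infusion time, which is why the two figures should be shown together.
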